### Data collection and management

#### Plans for assessment and collection of outcomes {18a}

We will use an electronic data collection form to capture the information using pre-existing forms. Participants will be followed up at 0.5, 1, 2, 3, 4, 5, 6, 12, 24, and 36 months. At each follow-up, routine blood tests, blood biochemistry and coagulation, serum lipid levels, and other related tests will be performed. All biochemical indicators, cervical vascular ultrasound, cardiac ultrasound, and electrocardiography will be performed at 6, 12, 24, and 36 months (see the Research flow chart).

#### Plans to promote participant retention and complete follow-up {18b}

There are no further strategies; those strategies were the same which were described in the improvement adherence to interventions.

#### Collection of basic information

Demographic information: age, sex, education, height, weight, CKD stage, body mass index, and comorbidities.Laboratory inspection: including routine blood tests, blood biochemical parameters, and ultrasonic examination.Blood and urine specimens will be obtained at baseline, 1, 6, 12, 24, and 36 months according to the research protocol requirements.Collection of adverse effects and complications: drug-related side effects and complications caused by the disease.

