
### Objectives {7}

This study aimed to determine the efficacy and safety of aspirin for preventing atherosclerosis in patients with CKD stages 3–5.
To evaluate the effect of antiplatelet therapy on accelerated atherosclerosis in patients with CKDTo evaluate whether antiplatelet therapy can reduce cardiovascular events or mortality in patients with CKDMoreover, antiplatelet therapy is considered to be safe for patients with CKD.

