**Secondary**		
The combined cardiovascular events	Incidence	**36** months
All-cause mortality	Incidence	**36** months
eGFR decreased by 50%	the proportion of eGFR decreased by 50%	**36** months
Safety outcomes	Numbers	**36** months

Carotid ultrasonography will be used to screen for atherosclerosis. The bilateral carotid arteries will be analyzed by color Doppler ultrasound at a frequency of 10 MHz using a linear array transducer (Model Vinno 70; VINNO Technology (Suzhou) Co., Ltd., China) by an experienced sonographer. A smooth carotid artery is considered normal. An atherosclerotic plaque is defined as a focal structure encroaching into the arterial lumen by at least 0.5 mm or 50% of the surrounding intima-media thickness (IMT) value or with a thickness of > 1.5 mm, as measured from the media-adventitia interface to the intima-lumen interface [21]. Both atherosclerotic plaques and IMT are indicators of carotid atherosclerosis. The carotid ultrasonography will be performed at 6, 12, 24, and 36 months to identify the status of carotid atherosclerosis.

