#### Safety outcomes

In the case of severe allergies, the drug should be discontinued immediately, and anti-allergy treatments and symptomatic treatments should be administered immediately.If a severe adverse event occurred, in addition to active treatment or rescue, the time, severity, duration, measures taken, and outcomes of serious adverse events should be recorded.If a treatment-related death occurred, the clinical study should be discontinued immediately, the event should be reported to the ethics committee of the clinical research unit as soon as possible, and the relevant information should be recorded and kept adequately in detail.All adverse events should be monitored until they are adequately resolved or until the patients’ condition stabilizes.

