##### Adverse event reporting and harms {22}

During the entire treatment and follow-up process, close attention should be paid to observing the adverse events or unanticipated toxic side effects (including symptoms, signs, and laboratory tests). Once an adverse event occurs, regardless of whether the event has a causal relationship with the drug, it should be addressed immediately. Moreover, the investigators should decide whether to terminate the study and conduct a safe visit based on the condition.

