However, the results of population-based studies remain controversial and inconclusive. Some studies suggested that aspirin can improve atherosclerosis, while other studies showed no difference compared with the placebo control group. Bavry et al. found that the use of aspirin could reduce the occurrence of endpoint events (cardiovascular death, myocardial infarction, or stroke) in the group with previous ischemic events; in the group without previous ischemic events, aspirin did not improve the occurrence of endpoint events [27]. Another study conducted by Ogawa et al. showed that treatment with low-dose aspirin did not prevent atherosclerotic events in patients with type 2 diabetes (including those with ischemic heart disease, stroke, and peripheral arterial disease) [28]. Only 100 patients were included, and the number of endpoint events in the aspirin group appeared to be lower but not statistically significant. A previous meta-analysis involving 10,117 patients suggested that there was no significant difference between the aspirin group and the blank control group in the reduction of all-cause mortality and atherosclerotic events [29]. However, in the CKD population, some studies suggested that low-dose aspirin (100 mg/day) can even increase the occurrence of CVD and CKD progression [30]. Therefore, the protective effect of aspirin in patients with CKD has not been determined.

In summary, if antiplatelet therapy is proven to be effective and safe for the prevention of atherosclerosis in the CKD population managed in a primary care setting in this pilot study, it will undoubtedly facilitate the development of a future definitive large RCT to determine the effect of antiplatelet therapy on hard, decisive endpoints (such as cardiovascular morbidity and mortality).

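### Safety is a joint aim, but its outcome is an undefined count, bleeding is not a named outcome, and the sections on adverse events disagree about which events are collected

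*Protocol article*

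**What the plan says.** All references are to the protocol article.

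- **Objectives {7}.** The opening sentence makes safety a joint aim: "This study aimed to determine the efficacy and safety of aspirin for preventing atherosclerosis in patients with CKD stages 3–5". The third listed item is phrased as a statement: "antiplatelet therapy is considered to be safe for patients with CKD".
- **Outcomes {12}, Table 1.** The safety row reads "Safety outcomes Numbers", at 36 months. No event type, unit or definition is given.
- **Safety outcomes.** Despite its heading, this section contains handling rules for severe allergy, for serious events and for a treatment-related death. It requires that "the time, severity, duration, measures taken, and outcomes of serious adverse events should be recorded", and adds: "All adverse events should be monitored until they are adequately resolved or until the patients’ condition stabilizes".
- **Collection of basic information.** The item on harms reads: "Collection of adverse effects and complications: drug-related side effects and complications caused by the disease".
- **Adverse event reporting and harms {22}.** Here the scope is wider: once an event occurs, "regardless of whether the event has a causal relationship with the drug, it should be addressed immediately".
- **Exclusion criteria.** Active bleeding, coagulation disorders and previous cerebral hemorrhage are exclusions. Plans for assessment {18a} adds blood counts and coagulation tests at each follow-up visit.
- **Statistical methods {20a}.** Chi-square comparisons are assigned to atherosclerosis, combined cardiovascular events, all-cause mortality and the eGFR endpoint. Safety appears only in a sentence fragment at the end, with no comparison attached.

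**The concern.** There are two defects in what the article states.

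First, the outcome that should answer the safety aim is fixed as a count of nothing in particular. It could be events or patients, of any kind and any seriousness. The protocol treats bleeding as a hazard when selecting patients but does not name it when measuring results. The combined cardiovascular endpoint contains no hemorrhagic event either.

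Second, a site that follows the data collection list would apply an attribution filter that the harms section does not apply. Attribution is a judgement. Filtering on it before the data are entered removes the chance to compare complete event counts between arms later.

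If carotid atherosclerosis turned out less frequent on aspirin, the result might be reported without a defined and fully captured measure of the harm to weigh against it.

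**Working it through.** The plan gives no safety figure to reproduce, so the check has two parts: a comparison of the texts, then an illustration of what the planned size can show.

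**1. The texts side by side**

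| Section | Which events | What is done with them |
|---|---|---|
| Collection of basic information | Drug-related side effects; complications of the disease | Collected |
| Safety outcomes | Serious events, no causality condition | Details recorded |
| Safety outcomes | All adverse events | Monitored until resolved or stable |
| Adverse event reporting {22} | All, whatever the cause | Observed and addressed |

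The route into the data for a bleed is then:

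- serious, any cause: recorded under Safety outcomes;
- non-serious, attributed to a drug (the wording does not say study drug) or to the disease: collected;
- non-serious, attributed to anything else: monitored and addressed, but no section says that it is recorded, and the collection list leaves it out.

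Only the third class is in doubt. It matters because minor and moderate bleeds may have a plausible local explanation.

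**2. What the planned size can show**

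Inputs from Sample size {14} and Sequence generation {16a}: 277 per arm, 36 months of treatment. The documents give no bleeding rate, so every rate below is an assumption.

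*Risk difference at 36 months, the measure proposed in the fix.* With p0 the placebo risk and p1 = 2 × p0 (assumed doubling), SE = √[(p0(1−p0) + p1(1−p1))/277] and the interval is (p1 − p0) ± 1.96 × SE. For p0 = 2%: SE = √[(0.0196 + 0.0384)/277] = 1.45 points, so the interval is 2.0 ± 2.8 points. Power is for a two-sided 5% test of two proportions.

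| p0 → p1 | Difference (points) | 95% CI (points) | Power |
|---|---|---|---|
| 1% → 2% | 1 | -1.0 to 3.0 | 16% |
| 2% → 4% | 2 | -0.8 to 4.8 | 28% |
| 3% → 6% | 3 | -0.4 to 6.4 | 40% |
| 5% → 10% | 5 | 0.6 to 9.4 | 61% |
| 10% → 20% | 10 | 4.1 to 15.9 | 91% |

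*Rate ratio, as a cross-check.* Patient-years per arm = 277 × 3 = 831. Expected placebo events b = rate × 831; aspirin events a = 1.5 × b (assumed ratio 1.5); SE of the log ratio = √(1/a + 1/b).

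| Placebo rate per 100 patient-years | Events, placebo v aspirin | 95% CI for ratio 1.5 |
|---|---|---|
| 0.5 | 4 v 6 | 0.4 to 5.2 |
| 1 | 8 v 12 | 0.6 to 3.6 |
| 2 | 17 v 25 | 0.8 to 2.8 |
| 3 | 25 v 37 | 0.9 to 2.5 |

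*No events in one arm.* The one-sided 95% upper bound is 1 − 0.05^(1/277) = 1.1%.

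These figures assume full follow-up. At the 251 per arm that the protocol's sample size section requires before its allowance for loss, power for a doubling from 2% falls from 28% to 26%, and the zero-event bound rises to 1.2%.

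**The case against.** The strongest reply is that the document as a whole gathers more than the data collection list suggests. Serious events are recorded without a causality condition, all adverse events are followed to resolution, deaths are a secondary outcome, and blood counts and coagulation are tested in both blinded arms. This stands. A reader might infer that adverse events are collected only when attributed to drug or disease, or that the safety aim cannot be answered at all. The documents support neither. A comparison between arms is possible; what is lacking is a defined event and one consistent collection rule.

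A second reply is that bleeding scales, form fields and safety tables usually sit in the full protocol or the SAP, which are not shown. This also stands, and nothing here counts their absence. The point rests on what the article does fix: an outcomes table, a section headed as safety outcomes, and a collection rule that conflicts with two other sections.

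Other tempting arguments do not hold:

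- The Discussion's remark that "low-dose aspirin (100 mg/day) can even increase the occurrence of CVD and CKD progression" concerns cardiovascular events and kidney decline. Both are measured as secondary outcomes, so it does not show unmeasured harm.
- The Discussion's closing words on efficacy and safety are conditional, describe a pilot study and look ahead to a larger trial. They commit to no claim of safety.
- The section on safety outcomes uses both severe and serious in the rule on recording. This is untidy, but the sentence evidently means one kind of event, and lost recording would be conjecture.
- The third objective reads as a drafting slip, because the opening sentence poses safety as a question. It still needs rewording.

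**Conclusion.** The point holds in this form. Safety is a joint aim; its tabulated outcome is undefined; bleeding is treated as a hazard but is not a named outcome; and the collection rule conflicts with the harms and safety sections. As written, a non-serious bleed attributed to another cause may or may not reach the data, depending on which section a site follows, and no bleeding comparison is pre-specified.

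The number of events lost this way cannot be estimated from the documents. The tables above do not measure it. They show a separate limit, which better capture would not remove: at assumed placebo risks of 1% to 3%, 277 per arm has 16% to 40% power to detect a doubling. A finding of no significant difference in bleeding would therefore not show that aspirin is safe. All bleeding rates, the doubling and the ratio of 1.5 are assumptions.

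**What to change.** 1. **Collection of basic information.** Collect all adverse events, with causality (and seriousness) as recorded fields, so that the rule agrees with Safety outcomes and Adverse event reporting {22}.
2. **Table 1 and Safety outcomes.** Replace the bare count with (a) the number of patients per arm with a bleeding event on a named published definition and (b) the number per arm with any serious adverse event, both to 36 months.
3. **Statistical methods {20a}.** Report each as a between-arm difference with its 95% confidence interval, and complete or delete the fragment on safety analysis.
4. **Objectives {7}.** Reword the third item as estimating the effect of aspirin on bleeding and other harms.
5. **Interpretation.** State in advance that the bleeding estimate will be imprecise at this sample size, and that lack of significance will not be read as evidence of safety.

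The cost is protocol wording, a bleeding page in the existing electronic form and slightly more data entry. No visits or patients are added. The Trial status section places the trial before recruitment, so at that stage the change could be made before any event is lost.

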#### Data management {19}

Once the trial is completed, the form will be printed for storage. We will link all data from observations using a unique identification number to facilitate data collection and accuracy.

#### Confidentiality {27}

The collection, storage, and analysis of study data will be carried out in compliance with the relevant data protection regulations during the trial period. Personal information will be replaced with a new identifier, which can only be accessed by the study physician and team member. The research data that need to be taken away from the research center should not contain the personal information of the participants. If necessary, the sponsor, government regulatory authority, or ethics committee may access the patients’ data from the study if required. However, this process will not reveal any information about the participants. After the trial, permission for further storage or use of the remaining specimen should be obtained from the participants, and informed consent will be signed by the participants. Finally, when the trial is finished, the study results will be published in an anonymous form.

#### Plans for collection, laboratory evaluation, and storage of biological specimens for genetic or molecular analysis in this trial/future use {33}

Not applicable for genetic or molecular analysis.

### Statistical analysis

#### Statistical methods for primary and secondary outcomes {20a}

For the primary outcome, the chi-square test will be performed to compare the occurrence rate of atherosclerosis at 1, 2, and 3 years of follow-up between the aspirin group and the placebo group. For the secondary outcome, the chi-square test will be performed to compare the combined cardiovascular events and all-cause mortality at 1, 2, and 3 years of follow-up between the aspirin group and the placebo group. Then, the decrease in eGFR will be computed using the value measured at the last follow-up minus the value measured at baseline; patients with a 50% decline in eGFR will be treated as patients who experienced an eGFR reduction of 50%. Similarly, the proportion of patients with an eGFR reduction of 50% between the aspirin group and the placebo group will be compared using the chi-square test. If the previous comparison did not reach a significant difference, the magnitude of decrease in eGFR between the two groups would be compared using two independent sample *t* tests or the Mann-Whitney *U* tests. In addition, multivariate competing-risk regression models will be used to assess the independent effect of treatments adjusted for age, sex, diabetes, serum lipid profiles, and phosphorus.

All statistical analyses will be performed using the SPSS software version 21.0 (IBM Corp., Armonk, NY, USA), and general data will be expressed as mean ± standard deviation. The variables with normal distribution and variance will be compared. One-way analysis of variance will be used for comparisons within groups. The SNK test will be used for multiple comparisons between groups. Pearson’s correlation analysis will be used for analyzing the correlation between variables. A nonparametric test will be used to analyze variables that do not meet the parameter test conditions. The Kruskal-Wallis *H* test or Mann-Whitney *U* test will be used for data comparison. Spearman’s correlation analysis will be used for correlation analysis. The chi-square test will be used for comparison. A *p* value of < 0.05 will be considered significant. A nonparametric test for multiple comparisons will be corrected using the Bonferroni method, *p* < 0.008, statistically significant safety analysis.

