#### Criteria for modifying or discontinuing intervention {11b}

Participants (1) who cannot tolerate aspirin, (2) in whom treatment was discontinued for more than 2 months due to various reasons, and (3) who will voluntarily withdraw from the study. Those who chose to withdraw from the study will receive appropriate treatment based on the judgment of each central investigator.

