#### Secondary outcomes

The combinations of cardiovascular events are as follows:
Acute ST-induced myocardial infarction: Evidence of myocardial ischemia, one of the following factors, and the rise or fall of the biochemical marker values (preferably cardiac troponin) with at least one value above the 99th percentile upper reference limit: (A) symptoms of ischemia, (B) new or presumed new significant ST-segment–T wave (ST–T) changes or new left bundle branch block, (C) development of pathological Q waves in the electrogram (ECG), (D) imaging evidence of new loss of viable myocardium or new regional wall motion abnormality, and (E) identification of an intracoronary thrombus on angiography or autopsy.Other acute coronary syndromes: In patients experiencing ischemic symptoms (pain at rest, shortness of breath, press-like discomfort, or progressive exacerbation of the above symptoms), rest or use of nitrates will not relieve these symptoms. On ECG, a transient or persistent ST-segment offset of 0.1 mV or above in one or more leads is usually observed.Congestive heart failure requiring hospitalization: Normal venous reflux is a clinical syndrome characterized by tissue hypoperfusion and pulmonary or systemic circulatory congestion marked by a decrease in cardiac output and an increase in ventricular filling pressure due to the presence of a primary cardiac damage and cardiac insufficiency.Severe arrhythmias: cardiac arrest and resuscitation, ventricular fibrillation, persistent ventricular tachycardia, paroxysmal ventricular tachycardia, primary atrial fibrillation or atrial flutter, severe sinus bradycardia, and complete atrioventricular block after a percutaneous coronary intervention or coronary artery bypass grafting. The occurrence of combined cardiovascular events will be recorded in every visit within the period of 3 years.All-cause mortality. The mortality from any other cause will be registered. These events will be collated during the 3-year follow-up.eGFR decreased by 50%. The eGFR will be calculated at every visit. When the trial is completed, patients in both groups whose eGFR decreased by 50% will be judged as experiencing a renal event.

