### Participant timeline {13}

The time schedule of enrollment, intervention assessments, and frequency of visits of all participants are shown in a schematic diagram (see the Research flow chart). The participants will be followed up at 0.5, 1, 2, 3, 4, 5, 6, 12, 24, and 36 months.

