### Sample size {14}

#### Sample size estimation

The sample was calculated as follows: $$ n=\frac{{\left({z}_{\alpha}\sqrt{2\overline{pq}}+{z}_{\beta}\sqrt{p1q1+p0q0}\right)}^2}{{\left(p1-p0\right)}^2} $$

In this study, p0 and p1 represent the estimated exposure rates of the control group and the experimental group, respectively, while *Z*_α_ and *Z*_β_ indicate the standard positive distribution boundaries. In the table, when *α* or *β* is equal to 0.05, its value is 1.96; when *α* or *β* is equal to 0.01, its value is 2.58. In this study, the incidence of p0 is above 40% [8]. After the intervention, p1 is expected to decrease by 15% compared with p0 (p1 = 25%). Let *α* = 0.05 (both sides), and *β* = 0.10. The calculated minimum sample size is 251; if 10% of the cases were lost to follow-up, the calculated sample size would be 277 for each group, and approximately 554 patients will be included in the trial.

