#### Methods in analysis to handle protocol non-adherence and any statistical methods to handle missing data {20c}

For missing data imputation, the last observation carried forward method will be used if the missing data met the following hypothesis: missing completely at random.

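### Cardiovascular events and deaths are compared by chi-square on yes/no status although 10% loss is allowed for; if loss differs by arm the result is biased, in a direction set by how leavers are counted

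*Protocol article*

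**What the plan says.** The section on statistical methods for primary and secondary outcomes {20a} names the between-arm test for two secondary outcomes: "the chi-square test will be performed to compare the combined cardiovascular events and all-cause mortality at 1, 2, and 3 years of follow-up". It names no Kaplan-Meier, log-rank or other unadjusted time-to-event comparison for them. It then adds, as a further analysis, that "multivariate competing-risk regression models will be used to assess the independent effect of treatments adjusted for age, sex, diabetes, serum lipid profiles, and phosphorus", without saying which outcome is modelled.

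Four other places bear on this:

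- Participant timeline {13} sets the same 36-month schedule for everyone: "The participants will be followed up at 0.5, 1, 2, 3, 4, 5, 6, 12, 24, and 36 months".
- Secondary outcomes: "The occurrence of combined cardiovascular events will be recorded in every visit within the period of 3 years". Deaths are likewise collated over the three years.
- Sample size estimation plans for the case "if 10% of the cases were lost to follow-up", with no split by arm.
- The missing-data section {20c} says "the last observation carried forward method will be used if the missing data met the following hypothesis: missing completely at random". The article states no rule for data that do not meet that condition.

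**The concern.** Both outcomes occur in continuous time, and the trial collects information on when they happen. A chi-square at a fixed year uses only whether an event has been seen by then, so it is straightforward only if everyone's status at that year is known. Follow-up is the same fixed length for all, so unequal time at risk can arise only through loss, withdrawal or death. The plan itself allows for loss.

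A patient who leaves without an event before year 3 must be put somewhere in the two-by-two table. Keeping the patient as event-free understates that arm's risk; removing the patient overstates it. If the arms lose different proportions, these errors do not cancel and a difference appears without any treatment effect.

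The protocol's objectives include whether treatment reduces cardiovascular events or mortality, and its discussion expects the results to inform a later definitive trial on such endpoints. A spurious difference of either sign would carry into that planning.

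**Working it through.** **Inputs from the article.** Overall loss is 10%, and there are 277 patients per arm (251 × 1.10 = 276.1, rounded up). Follow-up is 36 months. The test is two-sided at 5%. The article states no event rate for cardiovascular events or death, so there is no figure of its own to reproduce for these outcomes.

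**Assumptions.** The true 3-year risk R is the same in both arms and is varied from 5% to 30%. Event and departure hazards are constant, and departure is unrelated to event risk. The 10% loss is split as 15% in one arm and 5% in the other.

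**Formulas.** With L the loss proportion in an arm, put λT = −ln(1 − R) and γT = −ln(1 − L).

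- Leavers kept as event-free: observed proportion A = λ/(λ + γ) × (1 − exp(−(λ + γ)T)).
- Event-free leavers dropped: B = A / (A + S), where S = exp(−(λ + γ)T) is the proportion still followed and event-free at 36 months.

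**Worked case, R = 10%** (λT = 0.1054).

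- Arm with 15% loss: γT = 0.1625, sum 0.2679, S = 0.765. A = 0.1054/0.2679 × 0.235 = 0.0924. B = 0.0924/(0.0924 + 0.765) = 0.1078.
- Arm with 5% loss: γT = 0.0513, sum 0.1567, S = 0.855. A = 0.1054/0.1567 × 0.145 = 0.0975. B = 0.0975/(0.0975 + 0.855) = 0.1024.
- Risk ratio: 0.0924/0.0975 = 0.948 with leavers event-free; 0.1078/0.1024 = 1.053 with leavers dropped.
- Expected events with leavers event-free: 277 × 0.0924 = 25.6 against 277 × 0.0975 = 27.0.

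**Over the range of risks, 15% against 5% loss:**

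| True risk | Leavers event-free | Risk ratio | Type I error | Leavers dropped | Risk ratio |
|---|---|---|---|---|---|
| 5% | 4.62% vs 4.88% | 0.947 | 5.2% | 5.41% vs 5.12% | 1.056 |
| 10% | 9.24% vs 9.75% | 0.948 | 5.5% | 10.78% vs 10.24% | 1.053 |
| 20% | 18.52% vs 19.51% | 0.949 | 6.0% | 21.40% vs 20.43% | 1.047 |
| 30% | 27.82% vs 29.29% | 0.950 | 6.7% | 31.86% vs 30.58% | 1.042 |

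The type I error is a normal approximation to the chi-square test at 277 per arm, with leavers event-free.

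**Hand check.** If exits are spread evenly, a leaver contributes about half the time at risk, so the ratio with leavers event-free is roughly (1 − 0.15/2)/(1 − 0.05/2) = 0.925/0.975 = 0.949.

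**Equal loss, 10% in each arm.** The risk ratio is 1.00 under either handling, and the type I error is 5.0% with leavers event-free. Only the absolute rates move: at R = 10%, the observed rate is 9.5% with leavers event-free and 10.5% with leavers dropped.

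**Loss above plan, 30% against 10%.** The risk ratio is about 0.89 with leavers event-free (type I error 6.1% to 12.8%) and 1.10 to 1.13 with leavers dropped.

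An analysis that censors at departure has a hazard ratio of 1.00 in all these cases, but only because departure was assumed unrelated to event risk.

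**The case against.** The strongest defence is that everyone has the same 36-month schedule and the outcome table defines the metric as incidence at 36 months. Comparing proportions at a fixed horizon matches that and is valid when follow-up is complete. This stands; the problem comes only from incomplete follow-up. It is also right that the effect at the planned loss is small. At R = 10% the gap is 1.4 events, against a standard error of the difference of about √(2 × 277 × 0.095 × 0.905) = 6.9 events. These are secondary outcomes in a trial described as exploratory and as a pilot.

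The competing-risk regression does use time at risk, which softens the point. It does not remove it: the model is an addition to the chi-square, is covariate-adjusted and names no outcome, and for all-cause death there is no competing event.

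Three stronger readings are tempting, and the document does not support them:

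- A reader might infer that the arm whose patients leave earlier must show fewer events. That holds only if loss differs by arm and leavers stay in the denominator as event-free. Last observation carried forward would do that, but the article prescribes it only under missing completely at random, which exits caused by intolerance would not satisfy.
- A reader might count every criterion in section {11b} as loss of follow-up that is heavier on aspirin. The section covers modifying or discontinuing the intervention. Its first two items, "Participants (1) who cannot tolerate aspirin, (2) in whom treatment was discontinued for more than 2 months due to various reasons", concern stopping the drug and do not clearly end observation; only voluntary withdrawal plainly does. The efficacy analysis is described as intention-to-treat, and the article gives no loss by arm.
- A reader might fault chi-square because a patient who dies without a cardiovascular event is scored as event-free. Cumulative incidence also counts that patient as not having had the event, so this is not a defect peculiar to chi-square.

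**Conclusion.** The point holds for two secondary outcomes and is modest in size. The article fixes a test that cannot handle incomplete follow-up while planning for 10% loss and collecting events at every visit. Under no true effect and the assumed 15%/5% split, the apparent risk ratio is about 0.95 or 1.04 to 1.06 depending on how leavers are counted. With leavers event-free, the type I error is 5.2% to 6.7% instead of 5%. The sign is therefore not predictable from the article, and with equal loss there is no spurious difference. The distortion becomes large only if loss is well above plan and uneven. The primary conclusion on atherosclerosis does not rest on this.

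These figures depend on assumed event risks of 5% to 30%, an assumed split of loss, constant hazards and departure unrelated to event risk. The case for change is that the better methods cost almost nothing and use information the trial already gathers.

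**What to change.** In section {20a}, replace the chi-square as the main comparison for these two outcomes:

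- **All-cause mortality:** Kaplan-Meier curves, log-rank test and a Cox hazard ratio with 95% confidence interval, censored at last known vital status.
- **Combined cardiovascular events:** time to first event, cumulative incidence with death outside the composite as competing event, and a cause-specific hazard ratio.
- **Competing-risk regression:** name the cardiovascular composite as its outcome.
- **Chi-square at 1, 2 and 3 years:** supportive at most, with the counting of leavers stated.

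The cost is analysis wording, plus keeping event dates and last-contact dates in the database. No extra patients or visits are needed. Censoring still assumes that exit is non-informative, so the change removes the error from unequal time at risk but not bias from informative loss.
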